### Sample Selection

#### Overview

Mothers of children with a clinical diagnosis of ADHD [1] were identified by physicians working in hospitals or community clinics linked to the 3 research sites.

#### Inclusion Criteria

Mothers fluent in Japanese (reading and writing), parenting a child aged 6-12 years diagnosed with ADHD and attending elementary school, and for whom participation in a group-based behavioral intervention for the mother is not contraindicated were eligible for inclusion in the study. In addition, mothers of children diagnosed with ADHD and autism spectrum disorder were eligible to participate. Referring doctors were asked to exercise clinical judgment regarding mothers’ ability to understand the program content and their suitability to participate in a group program.

#### Exclusion Criteria

Limited pragmatic speech or a functional intellectual disability in the child would exclude a family from participating in the study. Current or recent (ie, within 2 months of the starting date of WPJ) participation in another parenting program would also exclude participation. Mothers of children receiving medication for the management of their ADHD symptoms were asked to keep their child’s medication constant throughout the study. Medication status changes will be recorded but will not result in the family being removed from the trial.

### Consent and Randomization

Physicians at the 3 hospital study sites confirmed the eligibility of the mothers of their patients with ADHD to participate in the study. They briefly explained WPJ and the requirements for research participation. Interested mothers were referred to the research site administrator for a detailed verbal and written explanation of the study procedures, including randomization to WPJ or TAU and the need to access the child’s medical records. Those who agreed to participate provided written consent for their own participation and their child’s participation. Written consent from teachers was obtained by mail. Children’s informed consent was obtained at the first laboratory assessment session.

Baseline outcome measures were obtained from mothers and teachers, including the Revised Five-Minute Speech Sample (R-FMSS) and the parent-child interaction task, before randomization to the study arm (Table 1 provides the full list of baseline measures). Teachers remained blind to family treatment group allocation. When sufficient participants were recruited at a site (a minimum of 12), they were randomized to the study arm, that is, block randomization at each site, using a computer random number generator operated by DD.

### Confidentiality

All participants were assigned an ID number at each site. Raw data were stored in locked storage at the collection sites. Only anonymized data were shared with researchers at the primary research site (Okinawa Institute of Science and Technology [OIST]) for database entry and analyses.

### Intervention

#### Arm 1: WPJ

Participants received a 13-session group-based intervention for parents of children with ADHD. This includes an orientation to the intervention, psychoeducation about ADHD, 4 sessions devoted to enhancing mothers’ psychological functioning adapted from the Parent Stress Management for ADHD program [14], followed by 8 sessions of behavior management based on the core components of the NFPP [18-22]. A summary of the session contents is presented in Table 2. Mothers and teachers completed outcome measures, including parent domain parenting stress, before randomization, after the intervention, and again after 3 months. Table 1 provides a complete list of the measures completed at each time point.

The 2-hour WPJ sessions are run by 2 group leaders at each site. Participants who are unable to attend a group session are invited to a 30-60 catch-up session before the next group session. The catch-up sessions are limited to a maximum of 2 sessions per participant. To maintain treatment fidelity, the groups are run according to the WPJ leader’s manual. At the end of each session, the leaders complete a checklist of the topics covered. Missed information is presented at the beginning of the next group session. Approximately 20% of the sessions delivered at each site will be randomly selected to confirm fidelity. These recordings will be reviewed independently against a checklist of the key and minor points to be covered in each session. The percentage of inclusion of major and minor points will be calculated and reported.

Group leaders receive supervision from SS, a certified trainer in both interventions that comprise WPJ. Supervision sessions for the first wave of groups lasted 60-120 minutes, depending on the experience and requirements of therapists. The frequency and duration of supervision were reduced to 60 minutes biweekly thereafter. Supervision of the first 2 treatment groups was conducted separately by site. Group supervision, that is, 3 sites together, was planned from the beginning of the third group. All supervision took place via electronic platforms.

**Table 2 table2:** Well Parent Japan session content.

Session	Content	Session function
1	Orientation to the program: What is ADHD^a^, part 1	Psychoeducation
2	Stress management, relaxation training	Mothers emotional health
3	Cognitive restructuring	Mothers emotional health
4	Problem solving	Mothers emotional health
5	Communication skills	Mothers emotional health
6	What is ADHD, part 2; Recruiting attention, positive communication, praise	Psychoeducation; New Forest Parenting Programme
7	Zone of proximal development, choices, clear messages, countdowns, using a timer	New Forest Parenting Programme
8	Review of session 7 skills, use of play	New Forest Parenting Programme
9	House rules, routine, boundaries, reward, and punishment	New Forest Parenting Programme
10	Review of session 9, review of ADHD symptoms	New Forest Parenting Programme
11	Temper tantrums (time out, quiet time), anticipating, avoiding conflict	New Forest Parenting Programme
12	Emotion and language, child relaxation	New Forest Parenting Programme
13	Social stories, mindfulness, wrap up session	New Forest Parenting Programme

^a^ADHD: attention-deficit/hyperactivity disorder.

#### Arm 2: TAU

TAU within the context of this trial may consist of many forms of intervention, including the following: medical and psychological examinations, pharmacological treatment, ADHD psychoeducation and parenting guidance, psychological counseling, play therapy for the child, group-based cognitive training for the child, telephone counseling for parents and teachers, and parent and teacher conferences or anything deemed clinically necessary. Mothers in the TAU arm had no contact with the research team from randomization until the treatment group (arm 1) completed the 13-week WPJ program. At this time, they attended a second laboratory assessment session with their child and completed all questionnaires. They completed the questionnaires again 3 months later. Site principal investigators will review and report the treatment options provided to all participating families (WPJ and TAU groups) through the referring hospitals during the trial period. This information will be included in the primary trial paper. The treatment group parents are given a 1000-yen (US $8.5) voucher per intervention session attended to help cover travel costs. All parents received a 2000-yen (US $17) voucher for the prelaboratory and postlaboratory assessment sessions and a further 1000-yen (US $8.5) voucher for the third cost-effectiveness interview. Teachers were given a 1000-yen (US $8.5) voucher each time they filled out the study questionnaires.

### Measurements

#### Diagnostic Measures

At baseline, autistic traits in the children were measured using the Autism-Spectrum Quotient [25]. This measure has excellent psychometric properties [26] and has been translated into Japanese and evaluated in both children [27] and adults [28]. The participating mothers’ ADHD traits are assessed using the Conners Adult ADHD Rating Scale [29] to better quantify the sample. The Japanese version of the scale has good psychometric properties [30].

#### Outcome Measures

##### Overview

Some of the measures (ie, the Vanderbilt Assessment Scale-Parent and Teacher, Parenting Sense of Competence Scale, Parental Locus of Control Scale, Family Strain Index, and Impairment Rating Scale) were translated into Japanese by the first author (SS) and independently back-translated by 2 bilingual US trained counseling psychologists.

The primary outcome measure was the mother’s reported parent domain parenting stress. This was assessed using the 78-item Japanese language version of the Parenting Stress Index [23]. The Parenting Stress Index assesses perceived stress in the parent-child dyad and yields the parent domain (sources of stress related to parent characteristics) and child domain stress (sources of stress related to child characteristics) scores and total stress score. The Japanese version of this measure has good psychometric properties [24].

Secondary outcome measures include parent and teacher ratings of the child’s behavior and mothers’ self-reports of their parenting style, competence, locus of control, family strain, mood, and objective measures of parent-child relationship quality. The measures are listed in Table 3.

All outcome measures, except for relationship quality, are administered at baseline, post treatment (week 14), and at the 3-month follow-up (week 26). Relationship quality measures are assessed at baseline and week 14 only. Teachers, but not parents, are blinded (probably) to parents’ group membership; that is, parents are asked not to discuss their group assignment with the child’s teacher.

**Table 3 table3:** Primary and secondary outcomes, measures, and raters.

Outcomes			Measures	Raters
**Primary**				
	Parent domain stress		Parent Stress Index	Mother
**Secondary**				
	**Child behavior**			
		ADHD^a^ symptoms	Swanson, Nolan, and Pelham Scale	Mother and teacher
		Impairment	Impairment Rating Scale	Mother
		Other	Vanderbilt Assessment Scale	Mother and teacher
	**Parenting practices or attitudes**			
		Management practices	Parenting Scale	Mother
		Locus of control	Parental Locus of Control	Mother
		Sense of competence	Parenting Sense of Competence	Mother
	**Emotional well-being**			
		Depression	Beck Depression Inventory-2	Mother
		Caregiver strain	Family Strain Index	Mother
		Child domain stress	Parent Stress Index	Mother
	**Mother-child relationship**			
		Parent-child interactions	Pasta making task; SCIFF^b^, SCIPD^c^	Independent coders
		Expressed emotion	Revised 5-minute speech sample	Independent coders

^a^ADHD: attention-deficit/hyperactivity disorder.

^b^SCIFF: System for Coding Interactions and Family Functioning.

^c^SCIPD: System for Coding Interactions in Parent-Child Dyads.

##### Parent and Teacher Ratings of Child Outcomes

The 26-item Swanson, Nolan, and Pelham Scale [31] is used to measure the child’s ADHD and oppositional defiant disorder symptoms. The Japanese translation has excellent psychometric properties [32]. The Parent and Teacher performance scales from the Vanderbilt Assessment Scale [33] are used to assess the child’s behavioral and academic performance at school. The 8-item Impairment Rating Scale [34] is used to assess parents’ perceptions of child impairment across a range of domains. This measure demonstrates acceptable psychometric properties including good temporal stability [34].

##### Parent Self-report Outcomes

Parenting practices are assessed using the 30-item Parenting Scale [35]. The Japanese version has a 2-factor solution and shows good internal consistency for overreactivity and low to moderate consistency for laxness in control and clinical samples [36]. The 17-item Parenting Sense of Competence Scale [37,38] is used to assess parenting competence or efficacy. The Japanese translation demonstrated adequate internal consistency in a normative Japanese sample [39]. The 47-item Parental Locus of Control Scale [40] is used to assess parents’ perceived locus of control in child-rearing situations. The internal consistency of this measure in our pilot RCT was good [22]. The Family Strain Index [41] is used to assess the effects of ADHD on families. Items 3 and 5 of this 6-item index have been revised to make the descriptions more culturally appropriate for Japanese parents. The second edition of the Beck Depression Inventory [42] is used to assess the mothers’ levels of depression. The Japanese translation is psychometrically robust and can be used to measure depressive symptoms in Japanese populations [43].

##### Parent-Child Relationship Outcomes

The quality of mother-child interactions is evaluated through direct observation of behavior during a cooperative task. Each mother-child pair works together for 15 minutes to make pasta using the ingredients and equipment supplied. The interaction is video recorded for later coding using selected parent and child codes from the System for Coding Interactions and Family Functioning [44] and the System for Coding Interactions in Parent-Child Dyads [22,45]. Maternal expressed emotion is measured using the R-FMSS [46]. Parents speak for 5 minutes, without interruption, about their child and their relationship. The R-FMSS has demonstrated excellent psychometric properties [46]. Trained raters, at OIST, blind to group membership and time point, will code the parent-child interactions and the R-FMSS.

#### Economic Evaluation Measures

Health economic costs are measured using a study-specific measure (Japanese Health Economic Costs [JHEC]) to collect all available information to estimate the child’s service utilization costs (medical treatment, education, nursing, and rehabilitation) and parents’ opportunity costs for their child’s care. The JHEC is administered at baseline, after the intervention, and at 3-month follow-up. The JHEC was developed with reference to the Client Service Receipt Inventory [47].

### Data Management Plan

All the participants are assigned an ID number at the trial site when they consent to participate in the study. This number is used on all questionnaires. Each site will maintain a list allowing them to link names and ID numbers.

Data collection at each clinical site is supported by a dedicated research assistant with oversight and support from the trial team at OIST. Anonymized questionnaire data will be scanned, password-protected, and saved in a shared Dropbox with the researchers at OIST. Video and audio recordings will be password-protected and saved in the same shared Dropbox. The OIST trial team will transfer the data from the shared Dropbox folder to secure electronic storage at OIST as soon as it is received. The OIST team will not have access to the data linking lists from any site. Data entry into a password-protected electronic database will be carried out by the trial staff at OIST.

Raw data (possibly containing names) will be maintained in secure storage at each site for 10 years after study completion. Access to these data is limited to the site principal investigator and dedicated research assistant. Once all data analyses are complete and manuscripts are prepared, OIST-maintained electronic password-locked files will be wiped. OIST will retain the anonymous password-protected data for 10 years after manuscript publication. GT will be responsible for the supervision of stored data.

Data analysis will be carried out by the trial statistician using an anonymized electronic database (see the Statistical Analysis section). Although there are no plans to make the data publicly available, requests for access to the data will be considered on a case-by-case basis, subject to Japanese law.

### Safety Considerations

Therapists are asked to record and report any potential adverse events using a standard template, and the importance of adverse events is highlighted during supervision sessions. Any adverse events are required to be reported to the approving ethics committees. In addition, all adverse events will be reported to the independent data and ethics monitor and will be evaluated, recorded, and discussed in the final paper.

### Statistical Analysis

#### Effectiveness Analyses

The analysis will be conducted on an intention-to-treat basis. Data will be explored first, and all variables will be summarized by treatment arm across measurement time, with mean (SD) presented for normally distributed measures, median (IQR) for skewed data, and frequency (%) for each observed level of categorical variables. Treatment effect estimates and their precision on the primary and secondary outcomes will be quantified through analysis of covariance modeling by means of multilevel modeling with baseline measure, arm, time, and interaction of arm × time included as covariates and participant as a level 2 analytical unit. As participants are recruited from different locations, the site will be included as a higher-level analytical unit if exploratory data analysis shows greater variability at the site level. Skewed outcome variables will be transformed for parameter modeling. Missing value information will be explored first to inform the missing value imputation by means of a multiple imputation procedure for multilevel data under a missing-at-random assumption. The results from the observed data will be examined to check the robustness of the treatment effect estimates sensitive to missingness. Stata statistical software (version 17; StataCorp) [48] will be used for data analysis. A statistical analysis plan, including all the analytical details, will be conducted before the data are locked for final analysis.

An independent data and ethics monitor is responsible for reviewing the trial progress and data analysis once data collection is complete. The monitor is independent of both the study team and sponsor OIST.

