**Results:**

Study funding was secured through a proof-of-concept grant in July 2018. Approval by the institutional review board for the data collection sites was obtained between 2017 and 2019. Data collection began in August 2019 and was completed in April 2022. Participant recruitment (N=124) was completed in May 2021. Effectiveness and cost-effectiveness analyses are expected to be completed by July 2022 and December 2022, respectively. These timelines are subject to change owing to the COVID-19 pandemic.

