### Sample Size Calculation

Parent domain parenting stress score at week 14 is the primary outcome measure and informed our sample size calculation. On the basis of the results of our pilot RCT [22], to detect a 0.5 standardized effect size at week 14 using 80% power at a 2-tailed .005 significance level, assuming the correlation between the baseline and follow-up measures is 0.35, 112 participants were required. After adjusting for a 15% attrition rate, the target sample size was inflated to 132.

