### Limitations

In recruiting through hospital clinics, the study does not include self-referred families in the community, possibly reducing the generalizability of the findings. Having clinic doctors (in Japan, the diagnosis of ADHD is limited to medical doctors; thus, referrals to the research were made by those responsible for the diagnosis of ADHD in the children) identify eligible families may have resulted in the referral of those dealing with more severe or comorbid ADHD, or mothers deemed most in need or most likely to benefit from participation in WPJ. Nonetheless, this is consistent with the aim of the research; that is, to evaluate WPJ within the Japanese child and adolescent mental health care system with a view toward future implementation of the intervention within this system. As a pragmatic trial, study site differences will be evaluated; however, we do not control for the effects of group leader skills on treatment outcomes. All group leaders are provided with the same training and are supervised by SS, which should help minimize differences in program delivery. The registration of the protocol was retrospective, and participant recruitment is now complete. No changes were made in the study protocol.

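### WPJ is delivered in groups, but neither the model nor the sample size has a group term; if outcomes correlate within groups, the standard error is too small

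*Protocol article*

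**What the plan says.** **Delivery.** Under Arm 1: WPJ, "Participants received a 13-session group-based intervention for parents of children with ADHD". The same section adds: "The 2-hour WPJ sessions are run by 2 group leaders at each site". Under Arm 2: TAU, control mothers join no WPJ group and have no contact with the research team until the WPJ arm has finished. Consent and Randomization describes individual randomization within a site once at least 12 mothers are available there. Trial Registration refers to three recruitment waves.

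**Model.** Effectiveness Analyses specifies a multilevel analysis of covariance with baseline, arm, time and arm by time "included as covariates and participant as a level 2 analytical unit". Site is a higher level only if exploratory analysis shows variability between sites. No group or leader level is named. Limitations states that "we do not control for the effects of group leader skills on treatment outcomes", and points to common training and supervision as a mitigation.

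**Sample size.** The inputs under Sample Size Calculation are effect size, power, significance level ("to detect a 0.5 standardized effect size at week 14 using 80% power at a 2-tailed .005 significance level"), correlation ("assuming the correlation between the baseline and follow-up measures is 0.35, 112 participants were required") and attrition ("After adjusting for a 15% attrition rate, the target sample size was inflated to 132"). There is no ICC and no design effect.

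**The concern.** This is a partially nested design. Randomization is individual, but one arm is then formed into groups whose members share 13 sessions, the same two leaders and each other's company. Any shared influence makes outcomes within a WPJ group alike, so those mothers carry less independent information than their number suggests. A participant-level random effect handles repeated measures on one mother; it does nothing for correlation between mothers.

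Site is no substitute. A site effect is common to both arms and all waves, whereas a group effect exists only in the WPJ arm and differs from wave to wave. It therefore feeds directly into the difference between arms.

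At stake are the confidence interval and P value for the primary outcome, and for secondary outcomes to the extent that they too correlate within groups. The error runs towards declaring WPJ effective.

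**Working it through.** **1. Reproduce the plan's figures.** Inputs from Sample Size Calculation: d = 0.5, r = 0.35, power 80%, attrition 15%. ANCOVA residual variance = 1 − 0.35² = 0.8775, so SD = 0.9367.

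- Two-sided .05: n per arm = 2 × 0.8775 × (1.960 + 0.842)² / 0.5² = 55.1, so 56. Total 112, and 112 / 0.85 = 131.8, so 132. Both match.
- Two-sided .005, as printed: 2 × 0.8775 × (2.807 + 0.842)² / 0.5² = 93.5, so 94. Total 188, which does not match.

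The figures thus follow from .05 with a design effect of 1. The printed .005 is a separate matter to be reconciled; .05 is used below as an assumption.

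**2. Group size (assumptions).** One WPJ group per site and wave gives 3 × 3 = 9 groups. With 1:1 allocation, 112 analysed gives 56 / 9 = 6.2 mothers per group. The 124 recruited (Abstract, Results) give 62 / 9 = 6.9 before attrition and 5.9 after 15% attrition. I use m = 6 and m = 7. The main Results section reports third-group suspensions, so there may be fewer than nine groups.

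**3. Formulas.** The ICC is assumed, from .01 to .10.

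- Design effect, WPJ arm: DE = 1 + (m − 1) × ICC. TAU arm: 1.
- Variance ratio for the arm difference: V = (1 + DE) / 2. SE ratio: √V.
- Actual type I error of a nominal 5% test: 2 × [1 − Φ(1.960 / √V)].
- Power at 56 per arm: Φ(0.5 / (0.1770 × √V) − 1.960), where 0.1770 = 0.9367 × √(2/56).
- N needed: 55.1 × V per arm, rounded up and doubled; then divided by 0.85.

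Example, m = 6, ICC .05: DE = 1.25, V = 1.125, √V = 1.061. Type I error = 2 × [1 − Φ(1.848)] = 6.5%. Power = Φ(2.663 − 1.960) = 75.9%.

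| ICC | m | DE | V | SE ratio | Type I error | Power at 112 | N needed (with attrition) |
|---|---|---|---|---|---|---|---|
| 0 | any | 1.00 | 1.000 | 1.000 | 5.0% | 80.6% | 112 (132) |
| .01 | 6 | 1.05 | 1.025 | 1.012 | 5.3% | 79.7% | 114 (135) |
| .01 | 7 | 1.06 | 1.030 | 1.015 | 5.3% | 79.5% | 114 (135) |
| .05 | 6 | 1.25 | 1.125 | 1.061 | 6.5% | 75.9% | 124 (146) |
| .05 | 7 | 1.30 | 1.150 | 1.072 | 6.8% | 75.0% | 128 (151) |
| .10 | 6 | 1.50 | 1.250 | 1.118 | 8.0% | 71.4% | 138 (163) |
| .10 | 7 | 1.60 | 1.300 | 1.140 | 8.6% | 69.7% | 144 (170) |

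**4. Does a site term help?** A simulation of ANCOVA at one follow-up (9 groups of 7, 8,000 runs, no group term) rejected a true null in 4.5%, 6.4% and 9.4% of runs at ICC 0, .05 and .10. With fixed site terms the rates were 5.2%, 6.6% and 9.3%. The excess remains.

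**5. What does a valid test cost?** The simplest test that respects the groups compares the arms within each site-by-wave batch and uses a t test on 9 − 1 = 8 degrees of freedom. Taking m = 6 and the same SEs with a noncentral t distribution, its power at 112 is about 70% at ICC 0, 65% at .05 and 60% at .10.

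**The case against.** A reader might infer that the planned analysis is known to give a false-positive rate above nominal. The documents do not support that. They report no ICC; at zero there is no inflation, and at .01 it is negligible. The harm is conditional, and its size rests on an assumed ICC.

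A reader might also infer that a group term has been ruled out. It has not. The article leaves the analytical details to a statistical analysis plan due before data lock, and that plan could add one. What stands is that the article does name the model's levels, omits this one, and says leader effects are not controlled for. Common training and supervision may reduce differences between leaders, but they do not remove correlation that comes from sharing sessions with the same mothers.

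Three further points have force:

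- Nine groups is an inference, and the suspensions make it uncertain.
- With so few groups, the group variance is poorly estimated. With nine groups of six and ICC .05, an ANOVA-type estimate is zero or negative in about 36% of samples, so a partially nested model needs a fallback.
- "Participant recruitment (N=124) was completed in May 2021", so a restated sample size cannot change enrolment. The power part of this point is one of disclosure.

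**Conclusion.** The point holds in conditional form. The named model has no WPJ-group level and the sample size has no design effect, so the planned precision is right only if outcomes are uncorrelated within groups. The protocol does not state that assumption, and the model as written cannot test it.

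On the assumptions in the working, the standard error is understated by a factor of 1.01 at ICC .01, 1.06 to 1.07 at .05 and 1.12 to 1.14 at .10. The effect on type I error and power runs from trivial to material over that range; it is not large enough to call the trial invalid. If the printed .005 were the intended level, the absolute error rates would be smaller but the relative excess larger: 0.89% at ICC .05 and 1.38% at .10 for m = 7. Power at 112 would then be about 51% before any clustering.

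**What to change.** Before data lock, specify in the statistical analysis plan:

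- a partially nested model with a random effect for WPJ group (site by wave) acting only in the WPJ arm, alongside the participant level, and with arm-specific residual variance if the data support it;
- REML estimation with small-sample degrees of freedom (Kenward-Roger or Satterthwaite);
- a fallback fixed in advance for a zero group-variance estimate or non-convergence, for example dropping the arm-specific residual variance first;
- reporting of the number and size of WPJ groups actually run and of the estimated group ICC;
- a restatement of power at the achieved sample size over an ICC range of about .01 to .10, in place of any further enrolment.

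The significance level in Sample Size Calculation should be reconciled at the same time, as a separate correction.

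The cost is some analysis-plan wording and a few lines of code. No new data are needed if group membership is on file. The real price is precision: with about nine groups, the interval widens and power falls, possibly by more than the design effect alone suggests, as the test on 8 degrees of freedom shows.

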## Methods

### Study Design

A multisite pragmatic RCT comparing the effectiveness and cost-effectiveness of WPJ (treatment arm) with TAU (control arm). Both arms will be tested at baseline, immediately after the intervention arm completes WPJ at week 14, and at 3 months follow-up; that is, week 26. The study is being carried out through Japanese child and adolescent mental health care services at three different hospital sites in Japan (Fukui, Fukuoka, and Okinawa). Table 1 lists the schedule of parent self-report, teacher, and objective assessments at each time point, whereas Figure 1 summarizes the study design and flow of participants through the trial.

**Table 1 table1:** Standard Protocol Items: Recommendations for Interventional Trials schedule.

Time point			Screening	Baseline	Intervention	Posttreatment (week 14)	3-month follow-up (week 26)

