### Trial Registration

The study was retrospectively registered with the International Standard Randomised Controlled Trial Number after the first of 3 waves of participant recruitment (trial registration number: ISRCTN66978270). Registration delay was an unintended consequence of ill health of one of the principal investigators, which disrupted study preparation. This oversight was identified after the first wave of participant recruitment and the trial was subsequently registered. Ethical approval for the trial, as described in the protocol, was obtained at all intervention sites before participant recruitment.

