## Results

The Training and Nurturing Support for Mothers (TRANSFORM) study began in July 2019 with therapist training, and a practice intervention group was run at each site between July 2019 and October 2019. Trial recruitment began in July 2019 and was completed in May 2021. The timeline of the study has been extended because of the limitations imposed by the COVID-19 pandemic. This included a 5-month postponement of the second treatment group (all 3 sites) and suspension of the third treatment group (2 sites). At the time of protocol submission, the suspension remained in place at 1 site. These suspensions will be reported in the final paper.

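### Site, the factor within which mothers were block-randomised, enters the model only after an undefined exploratory look and then as a random level with 3 sites; it should be a fixed effect in every model, preferably with randomisation batch or wave

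*Protocol article*

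**What the plan says.** The Effectiveness Analyses section of the protocol article specifies an analysis of covariance by multilevel modelling for the primary and secondary outcomes, "with baseline measure, arm, time, and interaction of arm × time included as covariates and participant as a level 2 analytical unit". On site it adds that "the site will be included as a higher-level analytical unit if exploratory data analysis shows greater variability at the site level". It does not say what the variability must exceed, how it is to be judged, or whether one decision serves all outcomes. Remaining detail is left to a statistical analysis plan to be written before data lock.

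Consent and Randomization says that once at least 12 mothers had been recruited at a site, "they were randomized to the study arm, that is, block randomization at each site". There are three hospital sites. Trial Registration dates registration "after the first of 3 waves of participant recruitment". The Intervention and Results sections refer to first, second and third treatment groups; the second was postponed by 5 months at all sites and the third was suspended at two. The Limitations section says that site differences will be evaluated but names no model term.

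**The concern.** When allocation is balanced within a factor, the analysis should normally carry that factor. Balance removes between-site differences from the treatment contrast. A model without site leaves those differences in the residual, so the reported standard error exceeds the true sampling variation of the estimate.

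The plan leaves this to the data, and three things are wrong with the rule as stated:

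- It has no criterion, so two analysts could follow it and fit different models.
- It covers primary and secondary outcomes alike, so the adjustment set could change from outcome to outcome.
- If triggered, it estimates a variance component from three sites, that is, on 2 degrees of freedom.

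The same reasoning extends to recruitment wave if randomisation was done batch by batch. The primary outcome is maternal stress, and the waves were separated by pandemic disruption, so wave is plausibly prognostic. At stake are some precision and a primary model that is fixed in advance.

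**Working it through.** **1. The plan's own figure.** Inputs from Sample Size Calculation: effect 0.5 SD, 80% power, baseline correlation 0.35, 112 required, 15% attrition. With 1:1 allocation, n per arm = 2(1 − r²)(z₁₋α/₂ + z₁₋β)²/d². At two-sided alpha 0.05: 2 × 0.8775 × (1.960 + 0.842)²/0.25 = 55.1, so 56 per arm and 112 in total; 112/0.85 = 131.8, rounded up to 132. Both figures reproduce. At the printed .005 the formula gives 94 per arm, 188 in total. That is a separate discrepancy; alpha 0.05 is used below because it matches the stated 112.

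**2. What three sites can say about site variance.** On 2 degrees of freedom, and even if site means were known without error, the normal-theory 95% interval for the between-site variance runs from 2/7.378 = 0.27 to 2/0.0506 = 39.5 times the estimate. An exploratory look at that quantity decides little.

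**3. The strata.** Three sites and three waves suggest up to 9 batches, averaging 124/9 ≈ 14 mothers, which fits the minimum of 12. Site × wave would use 8 degrees of freedom; site plus wave would use 2 + 2 = 4. No section uses the term site-by-wave, so this is inferred.

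**4. Simulation.** N = 112 in 9 batches of 12-13, 1:1 within batch, r = 0.35, ANCOVA at a single time point, test at 0.05, 4,000 runs per setting. ICCs are shares of the variance left after baseline adjustment. The article gives neither ICCs nor an inclusion test, so both are assumed; the conditional rule is represented by a site F-test at 0.05, with site then added as a fixed factor. In the last two columns the four figures are no adjustment / conditional rule / fixed site / fixed batch.

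| Site ICC, batch ICC | Site included by the rule | Type I error, % | Power at d = 0.5, % |
|---|---|---|---|
| 0, 0 | 5% | 4.9 / 5.0 / 5.0 / 5.0 | 79.0 / 79.0 / 79.1 / 79.1 |
| 0.05, 0 | 34-36% | 4.7 / 4.9 / 4.9 / 4.9 | 81.4 / 82.0 / 82.1 / 82.2 |
| 0.05, 0.05 | 42% | 4.2 / 4.6 / 4.6 / 5.1 | 80.9 / 82.0 / 82.1 / 82.8 |
| 0.10, 0.10 | 63% | 3.4 / 4.0 / 4.1 / 4.8 | 83.8 / 86.1 / 86.2 / 87.8 |
| 0, 0.10 | 25-26% | 3.8 / 3.9 / 3.9 / 4.8 | 80.0 / 80.6 / 80.6 / 82.2 |

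Monte Carlo standard errors are about √(0.8 × 0.2/4000) = 0.6 points for power and √(0.05 × 0.95/4000) = 0.3 points for type I error. The four analyses share the same simulated data within each run, so differences between them are more precise than that.

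**5. Reading the results.** Where there is batch variance, fixed batch gains over the conditional rule by 82.8 − 82.0 = 0.8, 87.8 − 86.1 = 1.7 and 82.2 − 80.6 = 1.6 points. Fixed site alone gains at most 0.1 point. With both ICCs at 0.10 and no treatment effect, the mean model standard error under the rule is 0.166 against a true SD of 0.159, about 4% too large; with fixed batch the two agree at 0.159. With no site or batch variance, fixed batch costs no measurable power (79.1% against 79.0%).

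**The case against.** The strongest reply is that a condensed article listing core terms, with detail deferred to a statistical analysis plan, has not excluded wave. That stands. Silence on wave is not a decision against it, so wave is a recommendation here and not an error. The reply does not cover site, because on site the article states a rule, and a statistical analysis plan that followed it would inherit the fault.

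It can also be said that the batches are inferred. Block size is not given, a batch might hold several blocks, and the number of batches per site is not stated. That stands too, and it is why site plus wave is as acceptable as site × wave.

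A reader might infer three stronger things that the material does not support:

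- **That choosing the model after seeing outcomes invalidates the primary p-value.** In the simulations type I error under the rule was 3.9-5.0%, so nominal to slightly conservative.
- **That the loss is larger.** With 124 × 0.85 = 105.4 analysed (52.7 per arm), power is 78.2% without adjustment. It is 80.3% or 82.3% if adjustment removes 5% or 10% of residual variance, for which the unadjusted standard error is 1/√(1 − v) = 1.026 or 1.054 times as large. But that compares adjustment with none at all, whereas the plan's rule already recovers part of the loss.
- **That the suspended groups call for an analysis without them.** That would drop randomised mothers, and the article does not say whether suspension came before or after randomisation.

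**Conclusion.** The point holds for site on the stated text: the rule has no criterion, leaves a design factor to the data, and proposes a random level on too few sites. The case for making site unconditional is prespecification and one common model across outcomes; on its own it buys almost no power. The measurable gain, 0.8 to 1.7 percentage points over the conditional rule, comes from the batch term. It depends on assumed ICCs of 0.05-0.10, on the assumed inclusion test, and on randomisation having run in batches per site. The error is on the cautious side, with standard errors somewhat too large. The treatment estimate is not biased if allocation is balanced within batch. This is a modest fault, worth correcting because correction is nearly free. Clustering by therapy group in the WPJ arm is a separate matter that these terms do not address.

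**What to change.** In the statistical analysis plan, before data lock, replace the conditional sentence with: *Site will be included as a fixed effect in every effectiveness model, whatever the exploratory results.* Drop site as a random level.

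Then confirm from the randomisation records how the batches were formed. If they ran in successive waves per site, also include randomisation batch or wave as a fixed effect, either as site plus wave or as site × wave.

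The cost is one or two sentences and 2 degrees of freedom for site alone, 4 for site plus wave, or about 8 for site × wave, out of roughly 105 analysed mothers. No new data are needed and the stated sample size is unchanged.
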